### Recruitment

3.5

Participants will be recruited via (1) clinicians' referrals, (2) referrals through in‐person meetings with traditional healers, and (3) if needed, advertisements through *Radio Television Guinea* and local Conakry‐based radio and television stations that reach most of the Guinean population. Traditional healers will be leveraged for recruitment purposes but will not serve as investigators or otherwise monitor study interventions. Most participants will be recruited by Guinean neurologists, as in preliminary studies.

## ASSIGNMENT OF INTERVENTIONS: BLINDING

4

### Who will be blinded?

4.1

Participants will be blinded to the primary study hypothesis. The Guinean site collaborators providing the intervention will be blinded to the primary study hypothesis.

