### Trial design

1.1

A randomized, double‐blinded clinical trial will be performed, including multiple healthcare facility sites in rural and urban Guinea but headquartered at the Ignace Deen Hospital in the capital city, Conakry. Two hundred PWE, clinically diagnosed by a Guinean and a U.S. neurologist, ages 18 years and above, will be enrolled and randomized 1:1 to (i) education and medication, or (ii) education and CCT (Figure 1). All participants will receive epilepsy education. Participants will be interviewed and examined by the Guinean–U.S. study team of neurologists at each visit. Follow‐up visits every 90 days until day 360 (approximately 1 calendar year) will assess the intervention on participants' clinical and socioeconomic outcomes. The recurring 90‐day follow‐up visits are considered beneficial to participants who may not access epilepsy care in any other way while also providing a sufficiently long timeline to study the sustainability of this intervention.

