### Intervention description

3.2

The education intervention will be given to each participant upon study enrollment in the form of a prerecorded, standardized video, made by the investigators, lasting approximately 30 min. The video is designed for people with low literacy and will answer the following basic questions: [What is a seizure? What is epilepsy? Why does epilepsy occur? Why is epilepsy a brain disorder? What works to treat epilepsy? What does not work to treat epilepsy? Why are ASMs important?] The video will be available in local languages (Sousou and Malinké), English, and French and shown on electronic tablets. A question‐and‐answer period, led by the study neurologists, will follow with no limitations on the amount of time. A flyer providing basic, written information on the education intervention will be given.

ASMs will be provided free of charge and prescribed for the participants in the study arm that includes the medication intervention. The ASM choice will be determined at the discretion of the neurologist in the context of the patient's history. There is no one best ASM for all patients, and most ASMs provide similar efficacy but dissimilar side effects and safety. There will be a total of seven possible ASMs to be used.

CCT will be conditioned on the return for follow‐up visits to the outpatient epilepsy clinic for scheduled appointments (±7 days every 90 days). Each visit for those in the CCT groups will entail the provision of 15 USD (given in the equivalent of Guinean Francs) to participants. This amount is anticipated to be a “nudge” (i.e., mildly incentivizing) as it exceeds the general cost of transportation for a return visit in the area (~5 USD on average) and ASM (which approximately costs ~4–10 USD for a monthly dosage in Guinea).^11^ It is important to note that this nudge will ensure participants in the CCT arm can afford the ASM, which enables study staff to assess outcomes from behavioral change rather than affordability considerations. The transfer will also be conditional on presence at visits, not on seizure outcomes. This ensures that participants are not penalized for aspects of their illness that are beyond their control.

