### Outcomes

3.3

The primary outcome of the study is adherence to neurology clinic appointments. This is defined as the number of appointments attended as scheduled and on time by the participant, as reported by the investigator.

Secondary outcomes are as follows:
Percent of PWE who achieve seizure freedom.Seizure frequency reduction: The percentage decrease in number of monthly seizures from baseline to the study endpoint of 360 days.

A complete list of outcomes can be found in Table 2.

**TABLE 2 epi412889-tbl-0002:** Primary, secondary, and exploratory outcomes of interest.

Outcome category	Outcome	Definition	Method of measuring
Primary	Adherence to Neurology Clinic Appointments	The number of appointments attended as scheduled and on time by the participant	Investigator reported
Secondary	Seizure freedom	% of PWE who achieve seizure freedom, or the ability to live without seizures of any type	Seizure diary counts
Secondary	Seizure frequency reduction	The percentage decrease in the number of monthly seizures from baseline to the study endpoint of 360 days	Seizure diary counts
Exploratory	Quality of life in epilepsy	A standardized scale and subjective report of physical, social, and psychological well‐being by a person with epilepsy	Patient/parent reported
Exploratory	Number of visits to traditional healers	Self‐reported number of visits to non‐allopathic providers for epilepsy management	Patient reported
Exploratory	Self‐reported adherence to ASMs	The number of pills left in the medication bottle, determined as a medication possession ratio	Investigator Counted
Exploratory	Stigma scale in epilepsy	A standardized scale and subjective report of stigma perceived by a person with epilepsy	Patient reported
Exploratory	Days attended at work or school	Self‐reported days attending school or work by a person with epilepsy of the past 90 days	Patient reported
Exploratory	Number of unintentional injuries due to seizures	Including burns, fractures, head injury, and related injuries in the past 90 days	Patient reported
Exploratory	Number of status epilepticus events	Reported by participant and family member in a log, articulating a seizure episode lasting >5 min	Patient reported

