### Data monitoring committee

7.1

The study will convene a Data Safety and Monitoring Board (DSMB) quarterly throughout the trial period. The DSMB will be composed of Guinean, U.S., and other global experts, including neurologists and biostatisticians, to review adverse events, trial progress, and data on the outcomes of interest. Adverse effects of the ASMs will be recorded. The DSMB may vote to unblind and withdraw a participant in the event of a serious adverse effect. Participants will be advised of any abnormal head imaging results performed by the study and referred for appropriate clinical care.

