## DISCUSSION

8

Our study provides a concrete plan to disaggregate issues contributing to the epilepsy treatment gap and target simple interventions addressing three major presumed reasons for the treatment gap: low epilepsy awareness, limited access to ASMs, and absolute poverty. Our approach provides a new pathway and model for clinicians and researchers to consider this problem. This study comes at a time when the international community is searching for effective mechanisms of alleviating the burden of epilepsy globally. The *Intersectoral Global Action Plan on Epilepsy and Other Neurological Disorders 2022–2031* emphasizes the need for concerted, interdisciplinary action to enhance epilepsy care and treatment in the near term (“Draft Intersectoral global action plan on epilepsy and other neurological disorders 2022–2031,”^7^). CCT interventions, if proven to be effective for epilepsy care, could serve as a powerful tool for these global efforts.

There are several strengths to this proposed study. The study design is both ethical and appropriate for low‐resource populations and, if successful, could be programmatically scaled to other locations. We also propose the first test of CCT, a method that has been used in other conditions, such as HIV/AIDS^31^ and TB,^32^ and in vaccination campaigns, to address low uptake. The use of CCT is controversial and untested in PWE but could serve as a poverty‐reduction intervention in addition to improving health outcomes among PWE. Though commonly tested for other health‐focused outcomes and in other regions, there is no published research on CCT programs in neurological disorders to our knowledge and only a limited sample of tested CCT interventions in West Africa.^33^, ^34^

There are also several limiting factors to the study design. Though participants are blinded to the hypothesis of the study, there is a possibility of participants disclosing information on their allocation to other participants, which would reduce allocation blindness. There is also a risk of differential attrition between the study arms. Several study outcomes are participant‐reported, which require clear and proactive communication with participants.

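### The trial is labelled double-blinded but only its hypothesis is concealed, so the investigator-reported attendance outcome is recorded without described masking while closely related attendance governs payment in the cash arm alone

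*Protocol article*

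**What the plan says.** The design label is in Section 1.1: "A randomized, double‐blinded clinical trial will be performed, including multiple healthcare facility sites in rural and urban Guinea". The Abstract uses the same label, and the Plain Language Summary calls the study blinded.

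Section 4.1, the only section on who is blinded, names two groups. For participants: "Participants will be blinded to the primary study hypothesis". For staff: "The Guinean site collaborators providing the intervention will be blinded to the primary study hypothesis". It mentions no concealment of allocation from anyone.

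Two later places treat allocation as masked. Section 7.1 states: "The DSMB may vote to unblind and withdraw a participant". The Discussion (Section 8) warns that participants might tell each other their allocation, "which would reduce allocation blindness".

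The interventions are in Section 3.2. For one arm: "ASMs will be provided free of charge and prescribed for the participants in the study arm that includes the medication intervention". The other arm receives 15 USD per visit, conditional on returning for scheduled appointments within 7 days either side. The same section then restates the condition more loosely, as being present at visits.

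The primary outcome (Section 3.3, Table 2) is the number of appointments kept on schedule and on time. Its method of measurement is "Investigator reported".

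**The concern.** Being unaware of a hypothesis and being unaware of an allocation are different protections. Double-blinding tells a reader that neither participants nor those treating or assessing them know the arm, and so that knowledge of the arm cannot influence what is recorded. Concealing the hypothesis gives no such assurance.

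The gap reaches the primary outcome. Whether a visit a few days off schedule counts as on time can be a judgement, and the article has it reported by investigators with no masking described. In the cash arm, closely related attendance also decides whether the participant is paid. In the free-medication arm, no timing condition is attached to the supply of drugs. Any leniency over a late visit thus has an extra motive in one arm only, and it would act in the direction that favours conditional cash in the two-sample non-inferiority test. Seizure diaries and patient-reported outcomes are also collected from people who know their arm, so the label matters beyond the primary outcome.

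**Working it through.** **Blinding: the statements side by side**

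| Place | What it implies about allocation |
|---|---|
| Abstract; Section 1.1 | Masked (double-blinded) |
| Plain Language Summary | Masked (blinded) |
| Section 4.1 | Not addressed; only the hypothesis is concealed |
| Section 3.2 | Visible: cash or free drugs, no dummy payment or placebo described |
| Section 7.1 | Masked, since it can be unblinded |
| Section 8 | Masked in part, yet participants are able to disclose their own allocation |

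These cannot all hold. A participant who is handed money, or is given drugs without charge, knows which it was, and so does whoever provides it. No sentence says outright that allocation is known; it follows from the interventions. The Discussion's worry about disclosure also presupposes it.

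**Outcome and payment**

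- Outcome: appointments attended on time, both arms, investigator-reported (Section 3.3).
- Payment: return for scheduled appointments, 7 days either side, cash arm only (Section 3.2).
- Visit window: 7 days either side, all participants (Section 5.2).

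The two conditions are close but are not expressly the same. *On time* is never equated with the 7-day window.

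**The plan's own figures (Section 6)**

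Bonferroni over two hypotheses gives 0.05/2 = 0.025, taken as one-sided. With 80% power, (1.960 + 0.842)² = 7.849.

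- One-sample, rate 0.90, margin 0.085: 0.90 × 0.10 × 7.849 / 0.085² = 97.8, so 98. Stated: 98.
- Two-sample, margin 0.12, with 90% assumed in the free-medication arm (not stated): 2 × 0.09 × 7.849 / 0.12² = 98.1, so 99. Stated: 99.

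At 100 per arm the two-sample power is 80.7%. The blinding point changes none of this.

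**How sensitive the comparison would be (illustration only)**

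The article gives no rate of misrecording. Assume that retention is scored yes/no as on-time attendance at day 360, with 100 per arm, free-medication retention of 90% and true cash retention exactly at the margin, 78%. If a share f of the cash arm's 22 missed or late visits is entered as on time, apparent cash retention is 0.78 + 0.22f. The chance of wrongly declaring non-inferiority is Φ[(0.12 − (0.90 − p)) / SE − 1.960], where p is the apparent cash rate and SE = √(0.90 × 0.10/100 + p(1 − p)/100).

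| f | Visits affected (22f) | p | False non-inferiority |
|---|---|---|---|
| 0% | 0 | 0.780 | 2.5% |
| 10% | 2.2 | 0.802 | 6.4% |
| 20% | 4.4 | 0.824 | 14.6% |
| 30% | 6.6 | 0.846 | 29.0% |

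The table shows only the direction and that small counts would matter under these assumptions. It is not an estimate for this trial.

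**The case against.** The strongest reply is that attendance is a dated event and not a rating, so open allocation matters little. Section 5.2 gives the same 7-day allowance to every participant, and Section 5.1 provides for data-quality training and weekly quality control by U.S. and Guinean staff. The article is also candid about what is concealed, both in Section 4.1 and in its limitations. All of this stands. It confines any bias to borderline visits, but it does not make the double-blinded label correct.

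Three stronger readings are tempting and are not supported.

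- *A reader might infer that the staff's on-time entry itself triggers payment.* No sentence says so, or says that whoever records attendance releases the cash. Section 3.2 also words the condition simply as presence at visits.
- *A reader might infer that five misrecorded visits would use 5 of the 12 points of margin (42%).* That needs all five to fall at day 360 and retention to mean on-time attendance, which Section 6 does not state. At the planned 90%, it would also mean half of the 10 expected failures in 100 were late visits entered as on time. Spread over 4 follow-up visits × 100 participants = 400, five errors are 5/400 = 1.25 points, about 10% of 12. If retention merely means having returned, they might count for nothing.
- *A reader might infer that the analysts are unmasked.* The article is silent, and the full protocol or analysis plan may settle it. A masked analyst could not in any case repair a date entered wrongly at the site.

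**Conclusion.** The concern holds as a mislabelled design with a possible, unquantified consequence for the primary outcome. The contradiction between the double-blinded label and Section 4.1 is explicit. That allocation is open is an inference, but a safe one given cash against drugs with no dummy described.

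The primary outcome is therefore recorded without described masking, while closely related attendance governs payment in one arm. Discretion over borderline late visits could favour cash in the non-inferiority comparison. The direction follows from the design; the size cannot be determined from the article. It depends on how many late visits occur, how they are recorded, and whether retention in Section 6 means on-time attendance. The document shows no actual bias and no established link between the entry and the payment. The sample size stands.

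**What to change.** Describe the trial throughout as randomised and open-label, with participants and site staff unaware of the primary hypothesis. Reconcile the Abstract, the Plain Language Summary and Sections 1.1, 4.1, 7.1 and 8 with that description. In particular, the reference to unblinding in Section 7.1 and the reference to allocation blindness in Section 8 should no longer presuppose masked allocation.

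Define on-time attendance by one rule applied identically in both arms: actual visit date minus scheduled date, within the 7-day window already stated in Section 5.2. Record the actual date when the participant attends, and check it in the weekly quality control of Section 5.1. Contemporaneous dates matter because a rule applied later cannot correct a date entered wrongly.

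The cost is a few wording changes, one definition and a check within an existing routine. No masking of the interventions and no new assessor is needed. The small downside is a less favourable design label.

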## DATA COLLECTION AND MANAGEMENT

5

### Plans for assessment, collection of outcomes, and data management

5.1

Data will be collected from the baseline visit and follow‐up visits (Table 3). An enrollment survey is provided in Appendix S2. All investigators will receive research ethics and data quality control training to ensure adherence to proper documentation and data collection. Data quality control measures will be implemented by the U.S. and Guinean staff on a weekly basis to ensure accuracy. Missing data will be addressed throughout the study. Use of REDCap™ with forced responses to progress to the next page will be used for surveys to avoid missingness. Other data points that are missing in a systematic way will be re‐evaluated for any clinical or cultural reasons. No data imputation will occur.

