The investigators will monitor participants' health throughout the study and re‐evaluate eligibility. For example, a woman may become pregnant or a participant may have a new illness (e.g., malaria). It will be ensured that all pregnant women have access to clinical care and an ASM (such as levetiracetam or lamotrigine) that is associated with the lowest fetal risk (whether she remains in the study or is withdrawn). Changes in health status and medical risk will be recorded, and the study team will adjudicate the event for administrative withdrawal of the participant. All withdrawn participants will have access to usual care following study discontinuation.

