## STATISTICAL METHODS

6

We choose a randomized two‐arm design with an equal sample size in the arm with the provision of conditional cash and the arm with the provision of free medication. Our sample size calculation is based on Hypothesis 1a.

To investigate Hypothesis 1a, we will first test the null hypothesis that the retention rate of the group with the provision of conditional cash is less than or equal to 90% using a non‐inferiority one‐sample proportion test. We will then test the null hypothesis that the provision of conditional cash will lead to a retention rate no less than the retention rate of free medication (controlling for medication type) using a noninferiority two‐sample proportion test. Since there are two hypotheses, in the sample calculation, we applied the Bonferroni correction to ensure a familywise error rate of 0.05.^27^ Given the existing studies and preliminary results, we expect that the retention rate of the group with the provision of conditional cash will have a retention rate higher than 90%. This reflects financial incentive clinical trials in other diseases where the intervention improves retention in care, particularly studied in HIV/AIDS.^28^, ^29^

Assuming it is 90%, to ensure a statistical power of 80%, with a noninferiority margin of 8.5%, the sample size of the arm with the conditional cash required is 98.^30^ We will then test the null hypothesis that the provision of conditional cash will lead to a retention rate no less than the retention rate of free ASMs using a noninferior two‐sample proportion test. Assuming the conditional cash group has 90% of PWE who will return at 12 months, with a noninferiority margin of 12%, to ensure statistical power of 80%, the sample size of the arm with the conditional cash required is 99.

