For Hypothesis 1b, we will use a one‐sample proportion test to test the null hypothesis that the percentage of PWE regularly taking ASMs at 12 months in the conditional cash arm is less than or equal to 85%, and we will use a two‐sample proportion test for the null hypothesis that the percentage of PWE regularly taking ASMs in the conditional cash arm is less than or equal to the percentage of PWE regularly taking ASMs in the free medication arm. For Hypothesis 1c, we will use a one‐sample proportion test to test the null hypothesis that the percentage of PWE with seizure freedom at 12 months in the conditional cash arm is less than or equal to 65%, and we will use a two‐sample proportion test for the null hypothesis that the percentage of seizure freedom in the conditional cash arm is less than or equal to the percentage of seizure freedom in the free medication arm.

To leverage the longitudinal observations collected during follow‐up visits at 90, 180, 270, and 360 days, we will use a generalized linear mixed effects model which allows us to study the association between multiple baseline variables (e.g., including the intervention options, education level, medication status, ASM type, distance to the study clinics) while accounting for the correlation between longitudinal observations.

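### The blanket ban on imputation restricts the 12-month ASM-use and seizure-freedom tests to participants with day-360 data, and attendance is the outcome the cash targets

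*Protocol article*

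**What the plan says.** - Plans for assessment, collection of outcomes, and data management: gaps in surveys are prevented by compulsory fields, and other systematic gaps are looked into. The paragraph then closes with "No data imputation will occur". Nothing confines that sentence to survey items.
- The same section and Table 3 place outcome collection at the study visits. Table 2 takes seizure freedom from diary counts and ASM adherence from counted pills.
- Statistical Methods: 1b and 1c each get a one-sample proportion test in the cash arm and a two-sample test against free medication. The one-sample null for 1c is "seizure freedom at 12 months in the conditional cash arm is less than or equal to 65" per cent; the one for 1b is 85%. No denominator is named for people without a 12-month visit.
- Objectives: retention is hypothesised to be similar in the two arms, at 90%.
- Discussion: "There is also a risk of differential attrition between the study arms".
- Eligibility criteria: health is re-evaluated after enrolment, and "the study team will adjudicate the event for administrative withdrawal of the participant". This is a second route to a missing 12-month value.
- Outcomes and Table 2: clinic attendance is primary, seizure freedom secondary, and pill-count adherence exploratory.

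**The concern.** A participant who does not attend at day 360 has no 12-month diary or pill count. With imputation ruled out, that person drops out of the proportion. Counting the person as a failure is itself a form of single imputation, so the rule as worded excludes that as well.

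Return to clinic is what the cash rewards, so being in the analysed set is a consequence of the intervention. Two things are at stake:

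- The one-sample tests can declare a target met among returners when it is not met among all randomised. This happens whenever non-returners do worse than returners, even if both arms retain equally well.
- If the arms differ in who returns, the two-sample test no longer compares the randomised groups, and the arm that loses more patients can look better.

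**Working it through.** **The plan's own figures first.** Statistical Methods sizes only Hypothesis 1a: "we applied the Bonferroni correction to ensure a familywise error rate of 0.05"; "to ensure a statistical power of 80%, with a noninferiority margin of 8.5%, the sample size of the arm with the conditional cash required is" 98; "Assuming the conditional cash group has 90% of PWE who will return at 12 months", and "with a noninferiority margin of 12%, to ensure statistical power of 80%, the sample size of the arm with the conditional cash required is 99". With one-sided 0.025 per test (0.05/2):

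- One-sample: n = 0.9 × 0.1 × (1.960 + 0.842)² / 0.085² = 97.8, rounded up to 98.
- Two-sample, 90% in both arms: n = 2 × 0.9 × 0.1 × (1.960 + 0.842)² / 0.12² = 98.1, rounded up to 99.

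Both reproduce. Non-return is itself the outcome there, so the imputation rule does not touch them.

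**Set-up.** Let r be the share with day-360 data, s the rate among them, and q the rate among the rest. The all-randomised rate is r·s + (1 − r)·q. From the article: r = 90%, targets of 65% (1c) and 85% (1b), and 200 participants allocated 1:1, so 100 per arm. Assumed: q, the free-medication retention where it differs from 90%, and a one-sided 5% level, since none is stated for 1b and 1c.

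**What 65% among returners means for all randomised (r = 0.90).**

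- q = 0: 0.90 × 0.65 = 58.5%
- q = 20%: 58.5 + 2.0 = 60.5%
- q = 40%: 58.5 + 4.0 = 62.5%
- q = 65%: 65.0%
- q = 100% (hard upper bound): 68.5%

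**One-sample false positives.** Set the true all-randomised rate exactly at the null. Then s = (null − 0.10·q)/0.90, with 90 people analysed (normal approximation).

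| Test | q | Rate in returners | Rejection at nominal 5% |
|---|---|---|---|
| 1c, null 65% | 0 | 72.2% | 41% |
| 1c, null 65% | 20% | 70.0% | 25% |
| 1c, null 65% | 40% | 67.8% | 13% |
| 1b, null 85% | 0 | 94.4% | 91% |
| 1b, null 85% | 40% | 90.0% | 35% |
| 1b, null 85% | 60% | 87.8% | 16% |

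At one-sided 2.5%, the 1c rejection rates are 29%, 16% and 7.5%.

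**Two-sample test, true seizure freedom 58.5% in both arms.**

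- Retention 90%/90%, same q in both arms: returner-only difference 0, rejection 5.0%.
- Cash 90%, free medication 78% (an assumed gap, equal in size to the 12-point margin): for q = 0, 20%, 40% the difference is −10.0, −6.6, −3.2 points, against cash. At q = 0, for example, 0.585/0.90 − 0.585/0.78 = 65.0% − 75.0%.
- Retention reversed: +10.0, +6.6, +3.2 points, with rejection in favour of cash 41%, 23%, 11%.

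**Bounds on an observed difference of 0, with 65% among returners in both arms.**

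- 90%/90%: each arm lies between 58.5% and 68.5%, so −10 to +10 points.
- Cash 90%, free medication 78%: cash 58.5% to 68.5%; free medication 0.78 × 0.65 = 50.7% to 50.7 + 22 = 72.7%. The difference runs from 58.5 − 72.7 = −14.2 to 68.5 − 50.7 = +17.8 points.

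**The case against.** **The restriction is an inference.** The article names no analysis set for 1b and 1c, and an unseen SAP may supply one. The ban also sits in a data-management paragraph largely about surveys. That is fair, but this is a stated rule and not a silence: a SAP that kept non-returners in the denominator would have to reconcile itself with an unrestricted sentence. One could define non-return as failure within the endpoint and not call it imputation, but the article does not do so.

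**Differential attrition is not forecast.** A reader might infer that the protocol expects the arms to differ in who returns. It does not say so. Objectives hypothesises similar 90% retention, and the 99 reproduces with equal rates. Statistical Methods expects cash to exceed 90% but gives no lower figure for free medication, and the Discussion calls differential attrition a risk. This objection stands, so the between-arm bias is conditional.

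**Other analyses and outcomes.** The mixed model uses all follow-up visits without imputing. It is presented as an association model, however, and is not the named test for 1b or 1c. The primary outcome is untouched, which limits the weight of the point.

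**Non-retention is not the same as missing data.** Someone who attends outside the ±7-day window may fail the attendance criterion and still bring a diary. The missing share could therefore be below 10%, and the effect correspondingly smaller.

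**Counting every non-return as failure has its own bias.** Some non-returners may be well, and the rule carries attendance differences into the seizure outcome. This stands, and is why that analysis should not be the only one.

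**Conclusion.** The point holds in a limited form. Followed as written, the plan tests 1b and 1c only in people with day-360 data. The firmest consequence is in the one-sample tests. At the protocol's own 90% retention, a true seizure-freedom rate of 65% would show as 67.8% to 72.2% among returners, and a nominal 5% test would reject 13% to 41% of the time. That rests on 40% down to 0% of non-returners being seizure-free; if they did as well as returners there would be no inflation.

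The two-sample comparison is a risk and not a demonstrated bias. It is sound if retention and non-returner outcomes are equal across arms, and at an assumed 90% versus 78% it is open to −14.2 to +17.8 points around an observed 0. A reader might take the 7.8-point gap (58.5% against 50.7%) as the worst case at that retention. It is only the case in which no non-returner in either arm is seizure-free, and the direction depends on which arm loses more.

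Nor do the documents support reading this as a threat to the trial's primary conclusion: Hypothesis 1a and the 98 and 99 are unaffected. The outcomes concerned are secondary (seizure freedom) and exploratory (pill-count adherence). The change should be made, but the design need not be.

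**What to change.** 1. Confine the no-imputation sentence to survey items.
2. For 1b and 1c, report results with all randomised participants in the denominator in two ways: multiple imputation using the earlier visits, and an analysis counting non-return as failure.
3. Keep the observed-case test beside them, with a tipping-point range showing what non-returner rates would overturn the conclusion.
4. Pre-specify which of these is the main analysis.
5. When rewording 1b, reconcile its target: Objectives gives 80%, while Statistical Methods tests against 85%.

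**Cost:** some wording and extra analysis, with no change to sample size or visits. The headline seizure-freedom figure will probably be less favourable. The failure-counting version brings attendance differences into the seizure result, so it should be read alongside the imputed one.
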